### Randomization and blinding

Stratified permuted block randomization will be used to balance gender and IBS types between two groups over time. Four strata is constructed according to sex and IBs types as follows:
Stratum1: Male patients with IBS-CStratum 2: Female patients with IBS-CStratum 3: Male patients with IBS-MStratum 4: Female patients with IBS-M

Within each stratum mentioned above, eligible patients will be randomly allocated in a ratio of 1:1 to receive propolis or placebo with a block size of 4. A block size of 4 is constructed six different arrangements (block) to assign patients to the trial groups as follows equally:
Block: Propolis, Propolis, Placebo, PlaceboBlock: Placebo, Placebo, Propolis, PropolisBlock: Placebo, Propolis, Placebo, PropolisBlock: Propolis, Placebo, Propolis, PlaceboBlock: Propolis, Placebo, Placebo, PropolisBlock: Placebo, Propolis, Propolis, Placebo

The sequence of the blocks mentioned above will be prepared for each stratum using a random numbers table. The study pharmacist will provide the placebo tablet similar to propolis tablet in color, odor, taste, shape, size, and weight, and they will be held in drug containers. All containers will be the same in terms of shape, color, odor, size, and weight and will be kept inside consecutively numbered, opaque, sealed envelopes, which are completely impermeable to light.

The trial-group assignments will be concealed from patients, physician, and investigators (enrolling, assessing, and analyzing) until the end of the study and data analysis, with the exception of the study pharmacist. The study pharmacist will provide a randomization list, sequentially numbered drug containers, and opaque and sealed envelopes.

### Study interventions

Fifty-two eligible patients will be randomly assigned to either the intervention group (*n* = 26) or the control group (*n* = 26). Patients in the intervention group will receive an identical propolis tablet containing 450 mg Iranian green propolis extract (100 mg polyphenol compounds and 67 mg flavonoids) twice a day, one tablet before lunch and one tablet before dinner, for 6 weeks. Propolis sample is obtained from honey bee colonies located in Rasht, the north area of Iran. Patients in the control group will receive an identical placebo tablet twice a day, before lunch and dinner, for 6 weeks. Propolis and placebo tablets will be similar in color, odor, taste, shape, size, and weight and will be produced by the School of Pharmacy, Mashhad University of Medical Sciences, Iran. Patients will be asked to continue their usual diet, physical activity, and medicines until intervention completion. Also, they will be instructed on how to use their supplements. Patients will be followed through weekly phone calls and intermediate visits (t_3_) to the clinic for assessing treatment compliance and adverse events. At the end of the trial (t_7_), participants will be informed of the usual dietary recommendations of IBS.

### Outcomes

The primary outcome of this clinical trial is the change in the severity of IBS from baseline to the sixth week of the intervention. The secondary outcomes of this clinical trial are the change in IBS quality of life, weight, and waist circumference from baseline to the sixth week of the intervention.

Demographic variables, including sex, age, race, education, income, marital status, smoking status, housing status, employment status, medical history, and family history, will be obtained from each participant at the beginning of the study (t_0_). Besides, for controlling of confounder factors, changes in dietary intakes, physical activity level, and anxiety will be evaluated in the current trial.

At the beginning of the trial, demographic information, food intakes, physical activity, weight, height, BMI, waist circumference, anxiety, IBS quality of life, and IBS severity will be collected by validated tools.

### Instruments

#### IBSSI

The study gastroenterologist who will be blinded to the treatment assignment will assess the IBS severity with the use of the IBS Severity Index (IBSSI). This scale is designed by Francis et al. [24]. This is a validated questionnaire with five sub-scales that measures the intensity and frequency (number of days) of abdominal pain, the intensity of abdominal distension, bowel movements satisfaction, and potential impact of IBS on the patient’s daily life during the last 10 days. The mean score of each section is a maximum of 100, and the total score of the questionnaire is a maximum of 500. Mild, moderate, and severe cases are displayed with scores of 75 to 175, 175 to 300, and more than 300, respectively. The internal correlation coefficient of 0.86 and Cronbach’s alpha of 0.69 have been reported for this questionnaire [25]. Although none of the IBS symptom severity tools have been completely validated, the above tool is currently reported to be the best tool used in most similar studies.

#### IBS-QOL

The study gastroenterologist who will be blinded to the treatment assignment will assess patients’ quality of life with the use of the IBS quality of life (IBS-QOL) questionnaire. This is a validated questionnaire with 34 questions and eight sub-scales including blame, interference with daily activities, physical imagery, health concerns, eating avoidance, social reactions, sexual problems, and communication issues that are in a range of degrees (never, rarely, to some extent, high, and severe). The minimum and maximum scores are 34 and 170; respectively. According to this questionnaire, lower scores indicate a higher quality of life. Daryani et al. validated this questionnaire. Its content validity has been confirmed by several medical groups, psychiatry, psychology, and epidemiology in Iran. The validity of the questionnaire was also evaluated using Cronbach’s alpha coefficient (*α* = 0.92), and the internal consistency coefficient of the questionnaire was excellent (*α* = 0.96). Also, its correlation coefficient with severity of symptoms was significant (*r* = 0.67; *P* value < 0.01) [26].

#### Anthropometrics

A trained nutritionist who will be blinded to the treatment assignment will assess anthropometric variables, including weight, height, body mass index (BMI), and waist circumference (WC) (Fig. 2). Weight will be measured using a digital Seca scale (Saca 831, Hamburg, Germany), with light clothing, to the nearest 100 g. Height will be measured using a portable stadiometer (Seca, Hamburg, Germany) in the standing position to the nearest 0.5 cm. Then, BMI will be calculated by dividing weight in kilograms by height in meters squared. WC will be measured without clothing at a level midway between the lower rib margin and the iliac crest at the end of exhalation and standing position using tape, to the nearest 0.5 cm.

**Fig. 2 Fig2:**
[figure not shown]
Schedule of enrollment, intervention, and assessments based on SPIRIT guidelines. Abbreviation: SPIRIT, Standard Protocol Items: Recommendations for Interventional Trials; IBS, irritable bowel syndrome; IBS-QOI, IBS quality of life; IBSSI, IBS Severity Index. Demographic variables, including sex, age, race, education, income, marital status, smoking status, housing status, employment status, medical history, and family history

#### Three-day food records

The change in dietary intakes will be measured using a 3-day food record (2 weekdays and 1 weekend day), as the “gold standard” for dietary assessment [27], at the beginning (t_0_), the middle (t_3_), and the end of the intervention (Fig. 2). A trained nutritionist who will be blinded to the treatment assignment will instruct patients on how to complete their food records and then will analyze completed food records. The amounts of each food item and drink will be converted to gram/day using Iranian Household Measures and then will be converted to the value of nutrients, such as FODMAPs (fermentable oligosaccharides, disaccharides, monosaccharides, and polyols), and calorie using Nutritionist IV software (First Databank Inc., Hearst Corp., San Bruno, CA, USA).

#### IPAQ

The change in physical activity will be measured using the international physical activity questionnaire (IPAQ) at the beginning and the end of the intervention. A trained nutritionist who will be blinded to the treatment assignment will instruct patients on how to complete their IPAQ and then will analysis completed IPAQ according to its guideline. IPAQ is an instrument designed for population surveillance of physical activity among adults which consists of seven questions about all types of physical activity as part of daily life performed in the last 7 days [28]. The Farsi-translated version of IPAQ was validated among the Iranian population by Moghaddam et al. with an excellent internal consistency (Cronbach’s alpha of 0.9). The reliability is reported by the Spearman-Brown correlation of 0.3 [29]. According to the scoring guideline of this questionnaire, the physical activity of the participants will be expressed as metabolic equivalents (MET)-minutes/week and four levels of activity, including vigorous, intermediate, walking, and sitting [30].

#### BAI

The change in anxiety will be measured using the Beck Anxiety Inventory (BAI) at the beginning and the end of the intervention (Fig. 2). A trained psychologist who will be blinded to the treatment assignment will instruct patients on how to complete their BAI questionnaire. This questionnaire is designed to measure anxiety with 21 items. Each item expresses one of the symptoms of anxiety that is commonly experienced by patients who are clinically anxious or those who are in anxious conditions [31]. The internal consistency coefficient of the questionnaire was excellent (Cronbach’s alpha of 0.92) [32]. The validity of the questionnaire showed good validity of the questionnaire by comparing the quantitative evaluation of clinical specialist with the scores of the subjects’ performance (*r* = 0.72; *P* value < 0.001) [33].

### Sample size calculation

We used Hern’s single-stage phase II methodology to calculate the sample size [34]. Based on results from other dietary supplements in patients with IBS [35] in which 15% of patients in the placebo group (*P*_0_) and 40% of patients in the intervention group (*P*_*1*_) had complete remission from symptoms of IBS, we need 22 patients in each trial group with a power of 80%. To compensate for withdrawal during follow-up, we increase the final sample size by 20%, to 26 patients in each group.

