## Materials and methods

### Study design

The current study is a prospective, single-center, randomized, double-blind, placebo-controlled clinical trial evaluating the efficacy of propolis supplementation in subjects with IBS. This clinical trial will be performed at the gastrointestinal clinic, a referral center for gastrointestinal diseases in Ahvaz, the southwest of Iran. All volunteers will provide written informed consent before participation in this randomized clinical trial.

The current trial is registered at the Iranian Registry of Clinical (ID: IRCT20190708044154N1). The study protocol was drafted and developed in accordance with the Standard Protocol Items: Recommendations for Interventional Trials (SPIRIT) 2013 checklist (Additional file 1). The protocol flow chart and timeline of the study are shown in Fig. 1 and Table 1, respectively. A protocol deviation is accidental and unintentional changes to the study protocol which have no significant impact on the study’s risk or benefit, subject’s rights, safety or welfare, and the integrity of the data [23]. The protocol deviations may result from the action of the patients or researchers. Examples of the protocol deviation for this study include:
A rescheduled study visitFailure to collect an ancillary self-report questionnaireSubject’s refusal to complete scheduled research activities.

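### The 22 per group comes from a single-arm design on complete remission, so the 80% power claim fails for the two-arm comparison and is not established for the primary outcome

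*Protocol article*

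**What the plan says.** The protocol's Study design section describes a "randomized, double-blind, placebo-controlled clinical trial evaluating the efficacy of propolis supplementation in subjects with IBS". Randomization and blinding sets 1:1 allocation to propolis or placebo. Under Outcomes, "The primary outcome of this clinical trial is the change in the severity of IBS" from baseline to week 6, measured by the IBSSI, whose total score has a maximum of 500 (Instruments, IBSSI).

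The Sample size calculation section rests on a "single-stage phase II methodology to calculate the sample size". Its inputs, from another dietary supplement in IBS, are that "15% of patients in the placebo group" (labelled P0) and "40% of patients in the intervention group" (labelled P1) "had complete remission from symptoms of IBS". It concludes that "we need 22 patients in each trial group with a power of 80" per cent, and then: "we increase the final sample size by 20%, to 26 patients in each group". The section gives no alpha, no sidedness, and no difference or SD for the IBSSI.

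Statistical analysis plans between-group tests, chi-square and Fisher's exact tests for frequencies, ANCOVA, and a logistic regression for improvement in the primary outcome. The significance threshold is P < 0.05. Complete remission is not defined or analysed anywhere in the protocol.

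**The concern.** There are two separate faults.

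- **Method.** A single-stage phase II design tests the response rate of one group against a fixed reference rate. Here the 15% plays that fixed role, although it will be estimated from a placebo arm no larger than the treated arm. Using the one-group total as the size of each of two groups leaves out the placebo arm's sampling error.
- **Endpoint.** The sizing endpoint is a binary remission rate, while the trial will be judged on the change in a continuous score. A power figure for the first says nothing about the second.

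At stake is how a null result is read. The protocol's abstract promises results whether positive or negative. Readers would take a non-significant result as coming from a trial with 80% power. For the difference it was sized on, the chance of detection is between about one third and just over one half.

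**Working it through.** **Inputs.** From Sample size calculation: p0 = 0.15, p1 = 0.40, power 0.80, 22 per group raised to 26. From Statistical analysis: significance at 0.05. Assumed, because the protocol does not say: one-sided 5% for the single-arm design and two-sided 5% for the between-group test. One-sided results are also shown.

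**1. Reproducing the 22.** Find the smallest n, with cut-off r, such that P(X ≥ r | n, 0.15) ≤ 0.05 and P(X ≥ r | n, 0.40) ≥ 0.80.

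| n | r | P(X ≥ r) at 15% | P(X ≥ r) at 40% |
|---|---|---|---|
| 20 | 7 | 0.0219 | 0.7500 |
| 21 | 7 | 0.0287 | 0.7998 |
| **22** | **7** | **0.0368** | **0.8416** |

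The answer is n = 22, which is the protocol's figure. It is the total for one arm against a fixed 15%.

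**2. Sample size for two arms on the same rates.** The pooled formula with p̄ = (0.15 + 0.40)/2 = 0.275 is

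n = {[1.960·√(2·0.275·0.725) + 0.842·√(0.15·0.85 + 0.40·0.60)] / 0.25}²
= [(1.238 + 0.510)/0.25]² = 48.9, so 49 per arm (57 with continuity correction).

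Other two-sided versions give 47 (unpooled) and 48 (arcsine). One-sided 5% versions give 37 (unpooled) to 47 (pooled with continuity correction). None gives 22. The pooled formula returns 22 only at one-sided alpha 0.15.

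**3. Power of the planned sizes for 15% versus 40%.** This is an exact enumeration of two independent binomials, summing the probability of every outcome pair that the test rejects.

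| Per arm | Chi-square, two-sided | Fisher, two-sided | Chi-square, one-sided |
|---|---|---|---|
| 22 | 46.6% | 35.0% | 61.8% |
| 26 | 55.3% | 40.8% | 66.4% |

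The pooled normal approximation agrees: 45.7% at 22 and 52.4% at 26, two-sided. With Fisher's test, power passes 80% between 55 per arm (79.8%) and 56 (80.8%). With 26 per arm and 15% on placebo, remission on propolis would have to be about 50% (chi-square) to 54% (Fisher) for 80% power.

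**4. The actual primary outcome.** With no SD or target difference, power for the IBSSI change cannot be computed. What can be computed is the standardised difference that an unadjusted two-sided 5% t test detects with 80% power:

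- 26 per arm: 0.79 SD
- 22 per arm: 0.86 SD

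For smaller effects, power with 26 per arm is 42% at 0.5 SD and 56% at 0.6 SD. With 22 per arm it is 37% and 49%.

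**The case against.** The strongest points on the other side are these.

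- **Sidedness and alpha are inferred.** The sample size section states neither, and P < 0.05 elsewhere does not say two-sided. This is correct and is marked as an assumption above. It does not rescue the claim, since one-sided chi-square power is still only 62% to 66%.
- **The analysed number may be 26, not 22.** The plan is intention-to-treat with multiple imputation, so 26 per arm is a fair basis, and chi-square power is then 55%. That is about 70% of the claimed power (55.3/80), so the fair summary is the range 35% to 55%. It is still far from 80%.
- **A binary form of the primary outcome is planned.** The abstract speaks of improvement in severity, and a logistic regression on improvement is foreseen. This narrows the endpoint mismatch but does not close it: improvement is not defined, and it is a different event from complete remission.
- **Power for the IBSSI change is unknown, not shown to be low.** This stands. A true effect of 0.8 SD or more would be detected with about 80% power or better at 26 per arm. ANCOVA could also help: if baseline IBSSI were a covariate (the plan does not list it) and its correlation with the final score were 0.5 (assumed), the detectable difference would be 0.79·√(1 − 0.25) ≈ 0.69 SD. The computed power deficit therefore concerns the remission comparison only.
- **The sample size was largely settled.** Recruitment began in July 2019, with completion expected around June 2020. That is why the fix leaves n alone. It does not make the power statement true.

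**Conclusion.** The concern holds and must be fixed. The 22 per group is a one-arm exact design (cut-off 7, alpha 0.037, power 0.842) applied to each arm of a two-arm comparison. On the protocol's own rates, power is 35% to 47% with 22 per arm and 41% to 55% with 26, depending on whether Fisher's test or chi-square is used. About 49 to 56 evaluable patients per arm would be needed for 80%. These figures assume two-sided 5%, and the conclusion is the same one-sided. For the change in IBSSI the protocol establishes no power at all. In an unadjusted t test, 80% is reached only for differences of about 0.79 SD (26 per arm) to 0.86 SD (22 per arm).

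**What to change.** Rewrite the Sample size calculation paragraph. Keep 52 patients, and delete the single-arm method and the 80% claim for 15% versus 40%. Suggested text:

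> With 26 patients per arm the trial has 80% power, at two-sided 5% and by unadjusted t test, to detect a between-group difference of 0.79 SD in the change in IBSSI (0.86 SD with 22 evaluable per arm). For complete remission of 15% versus 40%, power with 26 per arm is about 41% (Fisher) to 55% (chi-square). A non-significant result does not exclude effects smaller than these.

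State alpha and sidedness in the same paragraph. If the sponsor has an SD for the IBSSI change, convert the detectable difference to points (each 10 points of SD correspond to 7.9 points of difference at 26 per arm) so that readers can judge whether it is plausible.

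The cost is one reworded paragraph and a less favourable stated power. Allocation, tests and patient numbers do not change.

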### Safety evaluation

In this study, the dose of propolis supplementation was extrapolated from the study conducted by Sabuncuoglu et al. [18] in which the administration of propolis at a dose of 100 mg kg^−1^ improves the function of the GI tract and gut microbiota in rats. Based on the following formula for the conversion of animal dose to human [36] and reference body weight of 60 kg, the dose of propolis for a human is approximately 900 mg. At this dose of propolis, no adverse events were reported in the previous clinical trials.
$$ {\displaystyle \begin{array}{c}\mathrm{Human}\ \mathrm{equivalent}\ \mathrm{dose}\ \left(\mathrm{mg}/\mathrm{kg}\right)=\mathrm{Animal}\ \mathrm{dose}\left(\mathrm{mg}/\mathrm{kg}\right)\times \left({\mathrm{km}}_{\mathrm{Animal}}/{\mathrm{km}}_{\mathrm{Human}}\right)\\ {}\mathrm{Animal}\ \mathrm{dose}=100\ \mathrm{mg}/\mathrm{kg}\kern0.5em {\mathrm{km}}_{\mathrm{rat}}=6\kern0.5em {\mathrm{km}}_{\mathrm{Human}}=37\end{array}} $$

Patients will be asked to avoid taking the assigned supplement following the occurrence of adverse events and to immediately call the study physician or other investigators. One of the study researchers will be instructed to call the participants weekly by phone and ask them about experiencing any adverse events. Tabriz University of Medical Sciences is responsible to follow up on any adverse events and reports them to the Medical Ethics Committee of Tabriz University of Medical Sciences for decision making. If the reported adverse events are related to the consumed supplements, the study will be stopped and patients will be referred to a specialist for immediate treatment in which can be treated free of charge. Participants who are unwilling to continue collaborating on the study will be able to discontinue the trial at any time.

### Data management

One of the researchers will check the coding, security, and storage of data. Also, she/he will check data entry, and data values double times. If any patient reports the occurrence of adverse events, more information is needed for the decision making about excluding the patient from the study.According to the Medical Ethics Committee Criteria, unblinding is permissible in this situation, and we can specify whether the patient has received the propolis or placebo.

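### The rule permitting unblinding after any reported adverse event contradicts the blinding statement and allows exclusion to be decided with the arm known

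*Protocol article*

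**What the plan says.** The Randomization and blinding section of the protocol article makes a general promise: "The trial-group assignments will be concealed from patients, physician, and investigators (enrolling, assessing, and analyzing) until the end of the study and data analysis". One exception follows: "with the exception of the study pharmacist".

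The Data management section then states a rule for code breaks. The trigger and purpose are given together: "If any patient reports the occurrence of adverse events, more information is needed for the decision making about excluding the patient from the study". The permission follows, with reference to the criteria of the Medical Ethics Committee: "unblinding is permissible in this situation, and we can specify whether the patient has received the propolis or placebo".

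The Safety evaluation section has a researcher ask about adverse events in weekly phone calls. Patients who have an event are to "immediately call the study physician or other investigators".

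The Outcomes section defines the endpoint: "The primary outcome of this clinical trial is the change in the severity of IBS from baseline to the sixth week of the intervention". On who rates it, the IBSSI section says "The study gastroenterologist who will be blinded to the treatment assignment will assess the IBS severity", and the IBS-QOL section says the same of that scale. The Statistical analysis section makes intention-to-treat the primary approach, with multiple imputation for missing data.

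**The concern.** Breaking the code for one patient's safety is normal and is not at issue. Three features of this rule go further. Any reported event suffices, the purpose is a decision on trial participation rather than on the patient's care, and the recipients of the code are not limited.

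Two things are at stake. First, an exclusion decided with the arm known is a post-randomization decision that can depend on treatment. Adverse events may also differ between arms, so such decisions need not balance out. Second, the blinding of the person who rates a subjective symptom score rests on a promise that the code-break rule does not repeat or protect.

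**Working it through.** The plan gives no figure to reproduce on this point, and no formula applies. The check is a comparison of the sections.

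1. **Who stays blind, and until when.** Randomization and blinding: patients, the physician, and the enrolling, assessing and analyzing investigators, until data analysis is complete. The only exception is the pharmacist, who prepares the randomization list.
2. **Trigger for a break.** Data management: a patient's report of an adverse event. The article states no threshold of seriousness or clinical need. Because events are asked about every week, minor ones will also be elicited.
3. **Purpose.** Data management: deciding whether the patient is excluded. Treatment of the event is not mentioned there.
4. **Recipient.** Data management uses an unspecified first-person plural. It names no role and does not keep assessors or the analyst out. Items 1 and 4 cannot both hold as written: the researchers are either blind until after analysis, with the pharmacist alone excepted, or they may learn individual arms during the trial.
5. **Path to the analysis.** The Exclusion criteria section withdraws certain patients from follow-up, including those with sensitivity to the propolis supplement. If the arm is known when that is judged, the same complaint can be handled differently in the two arms. A patient withdrawn before week 6 has no observed primary outcome. Even if that patient stays in the analysis set with an imputed value, whether the outcome is missing then depends on a decision informed by the arm. This undermines the intention-to-treat comparison.
6. **Path to the rater.** Event reports go to the study physician or other investigators. The gastroenterologist rates IBSSI and IBS-QOL and is described as blinded. No section says that this person receives codes or takes the calls, and no section prevents it. The path is open but not shown to be used.
7. **Relatedness.** The Safety evaluation section makes stopping of the study depend on whether events are related to the supplements. Once a code is open, that judgement is no longer independent of the arm. The stopping rule itself is not assessed here.

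**The case against.** The strongest reply is that the Data management sentence is an ordinary patient-level exception, loosely worded. It says that unblinding is permissible, not that it happens. It refers to ethics committee criteria that are not shown and that may contain a threshold, a restriction on recipients and a logging rule. The Safety evaluation section also sends events to that committee for decision making, so the decision on exclusion may not lie with the study team. An article need not reproduce a full code-break procedure.

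Part of this stands. The lack of procedural detail is not a fault in itself. What remains is a rule the article does state, with its own trigger and purpose, which contradicts the single exception stated elsewhere.

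A reader might infer more, and the document does not support it:

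- *That every reported event opens the code.* The rule permits a break; it does not require one.
- *That the primary outcome will be rated unblinded.* The IBSSI and IBS-QOL sections both say the rater is blinded, and no section gives that person the code. The IBSSI content (pain, distension, bowel satisfaction, impact on life) also concerns the patient's own experience, and the rater's discretion over it is not described.
- *That many codes will be opened.* An assumed event rate of 10–30% would give 0.10 × 52 = 5.2 to 0.30 × 52 = 15.6 patients, but nothing in the document supports that rate. The Safety evaluation section says earlier trials at this dose reported no adverse events.
- *That one break exposes other patients.* In a block of 4 with two patients per arm, one known code leaves 1 of the other 3 on the same treatment, so the chance for any one of them moves from 1/2 to 1/3. This matters only to someone who has the code and can also work out block membership from stratum and enrolment order. With at least 52/4 = 13 blocks, it is a secondary matter.

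**Conclusion.** The point holds as a contradiction between stated rules. The Data management section lets an undefined group learn the arm after any patient-reported event in order to decide on exclusion. The Randomization and blinding section rules that out for everyone but the pharmacist. Followed as written, the rule permits exclusions made with the arm known, against the intention-to-treat primary analysis. It also leaves unprotected the rater blinding promised for IBSSI and IBS-QOL.

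That the primary outcome is actually rated with the arm known is a possibility left open, not a demonstrated defect. The size of any bias cannot be derived from the document. It depends on how many patients report events, how many codes are opened and who learns them, none of which is given, and the number of breaks could be near zero. The point should still be corrected because it bears on the primary comparison and the change is small.

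**What to change.** Reconcile the Randomization and blinding, IBSSI, IBS-QOL, Safety evaluation and Data management sections so that they state one rule:

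- Decisions on excluding a patient, and on whether an event is related to the supplement, are made without knowing the arm.
- A code break needed for a patient's safety goes from the pharmacist, who already prepares the list, only to those managing the event. It never goes to the outcome assessors or the analyst.
- The Randomization and blinding section names this exception beside the pharmacist.
- Each break is logged, and the number is reported by arm.

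The cost is modest but not nil. Decisions on non-urgent events would be made without knowing the arm, and a log has to be kept. The Study design section requires the department's agreement and ethics committee approval for amendments touching participants' safety. The Trial status section expected recruitment to be complete around 18 June 2020, and the article appeared on 5 August 2020. If the change comes too late to govern conduct, the trial report should still give the number of breaks by arm, who learned each code, and whether any exclusion followed.
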